### Trial design

This is a phase III, prospective, multi-center, double blind, randomized, placebo-controlled study. Eligible participants are randomized in a 1:1 allocation ratio to one of the two arms: an intervention arm, in which the participants receive dexamethasone according to the protocol, and a control arm in which they receive placebo.

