#### Comparative drug

Matching oral capsules are filled with maltodextrin to the same weight and are administered similarly.

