Participants will remain inpatients until the study drug is administered completely. Patients who ready to be discharged home earlier will have to finish the medication on their own. Protocol-mandated assessments will be performed according to the table of assessments (Table 
2). CT and/or MRI scans will be sent to a core laboratory and evaluated centrally in a triple-blinded way. Blood samples will be analyzed by the investigational laboratory locally.

**Table 2 T2:** Visit and assessment schedule

**VISITS**	**Screening**	**Post-procedure**	**Day 2 post operation**	**Day 3 of drug protocol**	**Until hospital discharge**	**Week 4 (16±7 days)**	**Week 12 (48±7 days)**	**Week 24**^ **1** ^**(96±7 days)**
Informed consent	x							
Medical history/demographics	x							
Procedure related information	x							
Randomization	x							
Concomitant medications^2^	x	x	x	x	x	x		
Physical examination	x				x			
Hematology, biochemistry, coagulation^3^	x				x(OD)^4^			
Urine pregnancy test	x							
Markwalder score	x				x (OD)	x	x	x
Blood glucose				x				
Intraocular pressure					x			
Neurological worsening events					x	x	x	
CT scan	x^5^		x^6^			x	x	x
Post-discharge information						x	x^7^	x
Adverse events			x	x	x^8^			
Serious adverse events	x^9^	x^9^	x	x	x	x	x^10^	

OD=once a day.

CT=computer tomography.

^1^Only in case of reoperation.

^2^Concomitant medications will be recorded in the CRF from 2 weeks prior to study drug start and up to the end of study drug medication.

^3^Blood will be analyzed locally and the results will be recorded in the CRF.

^4^Preoperative oral anticoagulated patients need a coagulation monitoring once a day to keep the parameters normal. In the same way are patients monitored with hyponatremia.

^5^If the baseline CT scan performed at a referral center, is of acceptable quality, and is available at the investigational site at the time of screening, it does not need to be repeated. However, if the only baseline CT scan available is a hardcopy film, then it must be repeated at the investigational site.

^6^CT scan to be performed during 48h post operation. In case of neurological worsening CT scans are repeated as required.

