### Randomization

Stratified randomization is done by using a computer randomization algorithm to generate balanced random samples (PASS 11, Hintze, J (2012). NCSS 8, NCSS, LLC. Kaysville, Utah, USA. http://www.ncss.com and Rosenberger, WF, and Lachin, JM 2002. *Randomization in Clinical Trials - Theory and Practice*. John Wiley & Sons. New York.) within each study site. Study site is the stratification variable for this randomization plan. Hence, the number of patients who receive verum medication is the same as the number of patients who receive a placebo in each study site, a 1:1 allocation ratio. Each patient receives a unique integer number ranging from 1 to 820 as an identification code, and this number will also be assigned to the corresponding medication kit. Each study site has a predefined set of patients to complete. In order to avoid consecutive recall of medication kits, the sequence in each study site is reordered by using random permutations.

The randomization plan will be implemented into an interactive web response system (IWRS) and hence the randomization is available for each study site. The investigators (or study staff) will interact with the system to receive the information as to which study group the patient is allocated, and which medication kit has to be used.

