### Data analysis

The primary endpoint is the rate of reoperation between 48 hours and 12 weeks after the initial evacuation of a chronic subdural hematoma. Mandatory reoperation during the first 48 hours is related to surgical complications. In such rare cases the patient will be excluded.

Evaluation of the Markwalder score will be done by computing crosstabulation tables and applying Pearson’s chi-square test. Data will be checked carefully for outliers and for normality based on the Kolmogrov-Smirnov test and Liliefors test. To evaluate the impact of dexamethasone on the thickness of the hematoma and other continuously distributed, metrically scaled variables, mixed models with treatment group as the independent factor and time as the repeated factor will be applied (if all assumptions for the model are met). Linearity will be assessed by Box Tidwell and log transformation. Corresponding planned contrasts together with 95% confidence intervals will be computed. If these variables do not fulfill the assumptions for parametric testing, nonparametric methods such as the bootstrap *t*-test, Kruskal-Wallis analysis of variance (ANOVA) with median tests and Friedman ANOVA with Wilcoxon matched-pairs test will be applied: 95% confidence intervals based on Pearson-Clopper values will be computed to estimate the reoperation rate in both groups. An unconditional test (Barnard’s test for superiority) for the ratio of these two proportions will be used. A *P*-value less than 5% will be considered statistically significant. All analyses will be done by one of the authors (WH) using STATISTICA 10 (Hill, T and Lewicki, P (2011). *STATISTICS: Methods and Applications*. StatSoft, Tulsa, OK, USA), StatXact 6.0 (Cytel Software Corporation (2003) Cytel Software Corporation, Cambridge MA, USA), NCSS 8 and PASS 11 Hintze, J (2012), NCSS 8, NCSS, LLC, Kaysville, UT, USA. (http://www.ncss.com).

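### As worded, the web randomisation system tells site staff the patient's study group, which contradicts the double-blind design

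*Protocol article*

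**What the plan says.** The Trial design section of the protocol article states: "This is a phase III, prospective, multi-center, double blind, randomized, placebo-controlled study". The Abstract also calls the trial double-blind. Under Comparative drug, the placebo is described so as to support this: "Matching oral capsules are filled with maltodextrin to the same weight and are administered similarly".

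The Randomization section then describes how allocation reaches the site. "The investigators (or study staff) will interact with the system", and they do so "to receive the information as to which study group the patient is allocated, and which medication kit has to be used". Two outputs are named, the group and the kit. The same section gives each patient a unique number from 1 to 820 and adds that "this number will also be assigned to the corresponding medication kit". It also fixes exact balance at every site: "Hence, the number of patients who receive verum medication is the same as the number of patients who receive a placebo in each study site".

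CT and MRI scans go to a core laboratory and are "evaluated centrally in a triple-blinded way" (Concomitant care). The endpoint is defined under Data analysis: "The primary endpoint is the rate of reoperation between 48 hours and 12 weeks after the initial evacuation".

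**The concern.** A double blind requires that the people who treat and assess patients do not know the arm. The Randomization section names site investigators and study staff as recipients of the group, and the group is not needed for dispensing because the kit number is enough.

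The primary endpoint is an operation. The Background section describes recurrence as the return of clinical and radiological symptoms leading to reoperation. The article gives no numerical threshold for that step and mentions no blinded adjudication. Knowledge of the arm could therefore influence whether a patient is reoperated. It could also influence Markwalder grading at the site and the attribution of adverse events. Attribution matters because the case for waiving certain serious adverse events (Waived SAEs; Methodology) relies on telling drug-related from disease-related events.

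There is a second consequence, which depends on the first. If past groups are visible and the site's list is exactly balanced, staff can form a view of the next allocation before they decide whom to enrol.

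**Working it through.** **1. The statements side by side**

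| Section | Content | Fits a double blind? |
|---|---|---|
| Abstract; Trial design | Trial called double blind | Yes |
| Comparative drug | Matched capsules of equal weight | Yes |
| Randomization, numbering | Patient and kit share one number, 1 to 820 | Yes; enough to dispense |
| Concomitant care | Blinded central reading of scans | Yes, but imaging only |
| Randomization, IWRS output | Group and kit given to investigators or study staff | No |

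No section says that the group is shown as a code or that the recipient is an unblinded pharmacist. The last row contradicts the first two.

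**2. Predictability, if groups are visible**

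Suppose a site's set has m patients, m/2 per arm, and staff have seen k allocations, of which a were dexamethasone. The chance that the next is dexamethasone is (m/2 − a)/(m − k). For the last patient m − k = 1, so the chance is 0 or 1. This assumes that staff know m. Without knowledge of past groups, a is unknown and the formula gives staff no advantage. Exact balance is therefore not a separate defect.

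**3. The plan's own power figure**

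Inputs from the Sample size section: 10% on placebo, ratio 2 (so 5% on verum), 370 per arm, one-sided score test, type I error 5%, stated power 83%. Exact binomial enumeration of the pooled score test against no difference gives 83.3%. The figure reproduces, and the IWRS wording does not affect it.

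**4. How many decisions would have to change**

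Expected events: 370 × 0.10 = 37 on placebo and 370 × 0.05 = 18.5 on verum. With 37 placebo events and y verum events,

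z = [(37 − y)/370] / √[p(1 − p) × 2/370], where p = (37 + y)/740.

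- y = 24: p = 0.0824, z = 0.0351/0.0202 = 1.74, above 1.645.
- y = 25: p = 0.0838, z = 0.0324/0.0204 = 1.59, below 1.645.

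Losing significance from the planned effect takes 25 − 19 = 6 or 25 − 18 = 7 changed decisions. Gaining it from no effect (37 versus 37) takes 37 − 24 = 13, which is 13/37 = 35% of the verum events.

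The boundary depends on the test:
- With a two-sided Barnard test of no difference it lies between 22 and 23 verum events (p = 0.043 and 0.070).
- With the null written in the Sample size section (ratio of 2 or less), a one-sided score test needs 10 or fewer (z = 1.80 at 10, 1.57 at 11).

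**5. An illustration resting on assumption**

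Take a true rate of 10% in both arms, 370 per arm, and suppose that knowledge of the arm led to a fraction of verum reoperations being withheld. The chance of a significant one-sided result against no difference would be:

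| Fraction withheld (assumed) | Chance of a significant result |
|---|---|
| 0% | 4.9% |
| 10% | 11.7% |
| 20% | 24.1% |
| 30% | 42.6% |

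The fractions are not in the article. The table shows sensitivity to such a bias and does not estimate it.

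**The case against.** The strongest reply is that this is loose drafting. The rest of the article describes a blinded operation. Capsules match and kits carry unique numbers, and each site's sequence is reordered so that kits are not called consecutively. Choice of comparator cites simpler blinding as a reason for choosing dexamethasone. Kit numbering and reordering would have little purpose if staff were told the arm, so the study group in that sentence may mean a coded assignment. This stands as a plausible account of what was intended. It does not remove the contradiction, because the sentence lists the group separately from the kit and nothing qualifies it.

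A reader might go further and infer that the blind was in fact broken, or that the surgeon who decides on reoperation is the person who sees the group. The article supports neither. One sentence in a condensed article does not show how the system was configured, and no section says who decides on reoperation or whether that person uses the IWRS. That site clinicians decide is a natural inference for a surgical endpoint, but it remains an inference. The requirement that symptoms and imaging findings reappear also limits discretion to some degree.

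A reader might also infer that a handful of altered decisions would overturn the result. That holds only for a result already at the boundary. From the planned effect it takes six or seven, and from no effect thirteen, under a one-sided test of no difference.

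Finally, details of block structure and code-break procedure are commonly left to the full protocol. Their absence here is no fault.

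**Conclusion.** The point holds as an internal contradiction. The Randomization section gives site staff the study group, while the Abstract, Trial design and Comparative drug sections describe a double-blind trial with matched placebo. Confidence in the contradiction is high, since it rests on the plain wording.

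The consequences are conditional. If the sentence is implemented literally, staff know the arm, and the primary endpoint, Markwalder grading and adverse-event attribution are open to bias; only the centrally read imaging keeps a stated safeguard. Predictable allocation follows only in that case. The size of any bias cannot be derived from the article: the counts of changed decisions assume 37 placebo events in 370 and a particular test, and the withholding fractions are assumed. The correction is still needed before the system is set up, because a site or vendor following the text as written would defeat the blind.

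**What to change.** Reword the sentence in the Randomization section so that investigators and study staff receive only the medication kit number from the IWRS. Add that the key linking kit to group is concealed from site staff and is opened only for emergency unblinding. Confirm that the IWRS display and user permissions match.

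If a masked code was meant all along, the rewording simply says so. The cost is one sentence and a display or permission setting. The sample size, power and allocation ratio do not change, and patients undergo no added procedure.

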### Data analysis

The primary endpoint is the rate of reoperation between 48 hours and 12 weeks after the initial evacuation of a chronic subdural hematoma. Mandatory reoperation during the first 48 hours is related to surgical complications. In such rare cases the patient will be excluded.

Evaluation of the Markwalder score will be done by computing crosstabulation tables and applying Pearson’s chi-square test. Data will be checked carefully for outliers and for normality based on the Kolmogrov-Smirnov test and Liliefors test. To evaluate the impact of dexamethasone on the thickness of the hematoma and other continuously distributed, metrically scaled variables, mixed models with treatment group as the independent factor and time as the repeated factor will be applied (if all assumptions for the model are met). Linearity will be assessed by Box Tidwell and log transformation. Corresponding planned contrasts together with 95% confidence intervals will be computed. If these variables do not fulfill the assumptions for parametric testing, nonparametric methods such as the bootstrap *t*-test, Kruskal-Wallis analysis of variance (ANOVA) with median tests and Friedman ANOVA with Wilcoxon matched-pairs test will be applied: 95% confidence intervals based on Pearson-Clopper values will be computed to estimate the reoperation rate in both groups. An unconditional test (Barnard’s test for superiority) for the ratio of these two proportions will be used. A *P*-value less than 5% will be considered statistically significant. All analyses will be done by one of the authors (WH) using STATISTICA 10 (Hill, T and Lewicki, P (2011). *STATISTICS: Methods and Applications*. StatSoft, Tulsa, OK, USA), StatXact 6.0 (Cytel Software Corporation (2003) Cytel Software Corporation, Cambridge MA, USA), NCSS 8 and PASS 11 Hintze, J (2012), NCSS 8, NCSS, LLC, Kaysville, UT, USA. (http://www.ncss.com).

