An important histopathological mechanism of origin is the high non-specific reaction potential of the capillary network in the inner dural sheet which, coming in contact with blood or fibrin degredation products, leads to the formation of a neomembrane. This mechanism is supported by the inflow of liquids like blood, later plasma and/or cerebrospinal fluid (CSF. Further progression is maintained by tissue activator (TA) exuding from the extremely vascularized membranes into the cavity, perpetuating a fibrin/fibrinogene mechanism leading to continuous microhemorrhages. Furthermore the automembrane developes inflammatory cells, like mastcells, eosinophiles, neutrophiles, monocyts, macrophages, endothelial cells and fibroblasts, being continuously activated and recruited. This constitutes a source of inflammatory angiogenic fibrinolytic and coagulation factors
[9].

The symptomatology consists of headache, neurological focal symptoms, aphasia, epilepsy and unconsciousness. After assessment of the symptoms a neurological classification can be made grading the patients from grade 0 to grade 4
[12]. The main diagnosis however, is done by imaging. Computerized tomography (CT) and magnetic resonance imaging (MRI) disclose monolateral or bilateral extracerebral fluid with more or less membranes separating the hematoma into chambers. Different classifications for both imaging tools are available
[13-15].

The primary therapeutic option is surgery. The standard procedure consists of a burr hole above the site of the lesion with or without irrigation. Santarius
[16] has proved that an insertion of a drain diminishes recurrence and mortality at 6 months after burr hole craniostomy. In cases of separation of the hematoma by thick layers, open craniotomy must be chosen to allow for evacuation of all chambers
[17]. Recurrence of the hematoma is defined as reappearance of the clinical and radiological symptoms and leads to reoperation.

The first remark about a nonsurgical treatment of cSDH was given by Ambrosetto
[18] in 1962. He described four patients, who received a conservative multimodal therapy in combination with corticosteroids: Their clinical symptoms regressed completely. Frati
[9] and Labadie

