#### Secondary objectives

The secondary objectives of the study are as follows: to measure the effect of dexamethasone on clinical outcome by the Markwalder score during a period of 12 weeks after surgery; the impact on radiologic signs of the hematoma, such as thickness, membranes and mass-demanding effect (midline-shift); to evaluate risk factors of the genesis and recurrence of cSDH in a prospective study design; risk of infectious complications, for example, pneumonia, urinary tract infection, ventriculitis, meningitis and encephalitis; dexamethasone-dependent severe psychiatric reactions; and death.

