### Inclusion criteria

The inclusion criteria are: 1) patients who are to undergo surgery for cSDH according to one or both of the following criteria: clinical symptomatology (Markwalder grade 1 to 4) with correlation to the cerebral lesion, or radiologic finding of cSDH with flattening of the underlying cortex and/or midline shift more than 5 mm; and 2) male or female patients aged over 25 years (inclusive).

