## Discussion of underlying literature

Despite 2,335 papers about cSDH identified in a recent PubMed search, treatment has not changed much. The main problem is the persistent recurrence. Glucocorticoids have a special capacity to block the inflammatory mechanism in the formation of the cSDH. They specifically inhibit lymphokins and prostaglandins and stimulate inflammatory inhibitors like lipocortin. Thus, the growing of neomembranes and neocapillaries is impaired
[3,19,20]. On the one hand cortisone reduces the expression of vascular epithelial growth factor (VEGF), which inhibits abnormal angiogenesis. On the other hand it induces the secretion of the inhibitor of plasminogen, so that the cycle of re-bleeding and lysis is decelerated
[3].

Several retrospective
[21,27,30-36] and two prospective
[25,28] studies about the use of cortisone in cSDH have been published. Two representative trials are discussed. In the first of the retrospective studies
[30] 122 patients were enrolled and divided into two groups: Subjects with a good neurological condition (Markwalder grading score (MGS) 0 to 2) were assigned to the dexamethasone protocol, whereas patients with MGS 3 to 4 were assigned to a surgical protocol. Of the 122 patients, 101 were on dexamethasone, and 22 of them ultimately required a surgical drain (21.8%{). A favorable outcome (MGS 0, 1, or 2) was obtained in 96% and 93.9% of those treated with dexamethasone and surgical drain, respectively. The overall mortality rate was 0.8% and readmissions related to the hematoma reached 14.7%. The study medication comprised administration of 4 mg dexamethasone every 8 hours for 3 days, tapering to 1 mg every 3 days. In total the medication lasted for 36 days.

The second study
[21] was of 142 patients treated with methylprednisolon and surgery, and 56 patient who only received surgery. The cortisone therapy decreased the risk of death threefold. Methylprednisolone was applied in a dosage of 0.5 mg/kg/day postoperatively for 30 days and was slowly tapered down subsequently.

The disadvantage of both cortisone protocols is their long duration and necessity of tapering the drug dose. There were medical complications in 27.8% of the dexamethasone group. Thus, the DRESH study has a drug application for 6 days only. The principal purpose is the proof of a practicable concomitant medication that has low incidence of side effects and is efficient, however.

Sun

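### The planned Pearson chi-square for the Markwalder score is valid, but ignores grade order and baseline and yields no effect estimate with an interval

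*Protocol article*

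**What the plan says.** The aim listed first under Secondary objectives is "to measure the effect of dexamethasone on clinical outcome by the Markwalder score during a period of 12 weeks after surgery".

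The Background describes the scale as "grading the patients from grade 0 to grade 4". The grades have a direction: the Discussion of underlying literature describes "Subjects with a good neurological condition (Markwalder grading score (MGS) 0 to 2" and counts the same range as a favorable outcome.

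A grade is available at entry. One of the two routes into the trial is "clinical symptomatology (Markwalder grade 1 to 4) with correlation to the cerebral lesion"; the other is radiologic. Table 2 schedules the score at screening, daily until discharge, at weeks 4 and 12, and at week 24 after a reoperation.

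The Data analysis section gives one method for this outcome: "Evaluation of the Markwalder score will be done by computing crosstabulation tables", tested with Pearson's chi-square. The threshold for all tests is a P-value "less than 5% will be considered statistically significant". The same section gives mixed models over time, contrasts with 95% confidence intervals and rank-based fallbacks, but only for hematoma thickness and other continuous variables.

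**The concern.** The method is named, so this is a choice the protocol makes and not detail left to an analysis plan. The choice fits the objective poorly in four respects.

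- **Order.** Pearson's statistic is unchanged if the grade columns are permuted or the arms are swapped. The information that grade 1 is better than grade 3 is not used.
- **Baseline.** Patients may enter at any of grades 1 to 4, or on radiology alone. The screening grade plays no part in the test.
- **Repeated scores.** The objective covers 12 weeks and the score is taken repeatedly, but no time point or longitudinal structure is attached to the test.
- **Estimate.** The objective is to measure an effect. A chi-square P-value does not do that, whereas reoperation rates and continuous outcomes do receive confidence intervals.

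At stake are the efficiency and interpretability of the trial's clinical-status outcome.

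**Working it through.** **The plan's own figure.** There is none for the Markwalder score: no distribution, target effect or power. The only power stated is 83%, for reoperation. With 10% versus 5%, 370 per arm, one-sided 5% and equal rates as the null, exact enumeration of the score test gives 83.3%, so it reproduces. It has no bearing on this outcome.

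**Step 1: cost of the extra degrees of freedom.** Inputs: five grades (Background), hence up to 4 df in a 2 × 5 table, and the 5% level (Data analysis), taken as two-sided. Assumptions: a roughly proportional shift, which a 1-df ordered test captures fully, and 80% power for that test.

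Noncentrality: λ = (1.96 + 0.8416)² = 7.85.

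Power at k df = P(noncentral χ² with k df and λ exceeds the central 95% point with k df).

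| Occupied grades | df | Power of chi-square | Loss against 80% |
|---|---|---|---|
| 5 | 4 | 59.5% | 20.5 points |
| 4 | 3 | 64.5% | 15.5 points |
| 3 | 2 | 70.9% | 9.1 points |

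At 4 df the loss depends on the power of the ordered test: 19.2 points at 50%, 21.8 at 70%, 16.0 at 90% and 11.3 at 95%.

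**Step 2: simulation.** 20,000 trials per setting compared the 2 × 5 Pearson chi-square with a tie-corrected Wilcoxon test. The 370 per arm comes from the Sample size section. The placebo grade distributions and odds ratios (OR) are assumptions. Cells show chi-square / Wilcoxon power, with the loss in points taken before rounding.

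| Assumed placebo grades 0–4 (%) | OR 1.2 | OR 1.5 | OR 2.0 |
|---|---|---|---|
| 50/30/12/5/3 | 15.1 / 25.7 (10.6) | 61.4 / 81.8 (20.3) | 98.1 / 99.7 (1.6) |
| 70/20/6/2/2 | 12.2 / 20.7 (8.5) | 45.9 / 68.0 (22.1) | 91.2 / 97.8 (6.6) |
| 30/35/20/10/5 | 16.3 / 28.1 (11.8) | 66.8 / 85.7 (18.8) | 99.3 / 100.0 (0.7) |
| 20/20/20/20/20 | 16.8 / 28.8 (12.0) | 70.0 / 87.4 (17.4) | 99.5 / 100.0 (0.4) |

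Over all runs, including 410 per arm and odds ratios from 1.2 to 2.0, the loss runs from 0.2 to 22.5 points.

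**Step 3: validity.** With no effect (OR 1.0), the chi-square rejected in 4.8% to 5.2% of trials.

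**Step 4: effects that are not a shift.** From 50/30/12/5/3, halve grades 3 and 4 and move those patients to grade 2, giving 50/30/16/2.5/1.5. Chi-square power is 53.7% and Wilcoxon 5.4%. With movement in both directions (56/22/10/6/6) the figures are 74.3% and 12.5%.

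**Baseline.** The gain from adjustment depends on the correlation between baseline and outcome grade. The protocol does not give it, so no figure is attached.

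**The case against.** The strongest reply is that the 2 × 5 table is inferred. The protocol gives neither the dimensions nor the visit, and its literature discussion itself groups grades 0 to 2. Grouping, time point and covariates are often left to a fuller document. This stands as a limit on the size: each merged grade reduces the loss, and a two-category split would remove the degrees-of-freedom penalty altogether, at the price of discarding differences within each group. It does not remove the point, because the named test uses neither order nor baseline and supplies no interval for the effect.

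A reader might infer four stronger criticisms. The documents support none of them.

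- *The trial loses 20 points of power on this outcome.* That needs five occupied grades, a roughly proportional shift and mid-range power. The protocol states none of these.
- *Sparse high grades invalidate the test.* With an assumed control distribution of 55/30/10/3/2%, an expected count below 5 occurred in about 20% of trials. Yet none had an expected count below 1, fewer than 1% had more than two of ten cells below 5, and the type I error was 4.7%.
- *The test can be significant without benefit, so it misleads.* Any two-sided test, including an ordinal one, can be significant for harm.
- *The effect cannot be read at all.* The cross-tables show grade proportions by arm. What is missing is a summary estimate with an interval.

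The reversal in Step 4 also stands: an ordered test is not uniformly better.

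**Conclusion.** The point holds as a matter of efficiency and interpretability on one secondary outcome. The analysis is not invalid, and the primary endpoint and sample size are untouched.

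The size is conditional. Where an ordered test would have 80% power under a roughly proportional shift, the chi-square has about 60% with five occupied grades, 64.5% with four and 71% with three. Across the assumed shifts the loss is between near 0 and about 22 points; it is smallest for large effects and reverses for some effects that are not shifts. These figures concern order only. The lack of an effect estimate with an interval does not depend on any of these assumptions.

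**What to change.** Name as the test a proportional-odds model of the Markwalder grade on treatment, adjusted for baseline grade and study site (the randomization stratum). Make week 12 the main time point, and either include the week-4 score as a repeated measure or report it alongside. Report the common odds ratio with its 95% confidence interval.

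Keep this model as the test whatever a proportionality check shows, so that the choice of test does not depend on the data. Add a site-stratified Wilcoxon (van Elteren) test as a sensitivity analysis, and retain the cross-tables as description.

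The cost is wording, settled before unblinding; no new visits, patients or measurements are needed. There are two downsides. If proportionality fails, the common odds ratio is only an average summary. The ordered test is also less sensitive to effects confined to a few grades or running in opposite directions, which is one reason to keep the tables in view.
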